**Flow of participants.**

### Recruitment

This study will be conducted in the Department of Ophthalmology, Xinjiang Uygur Autonomous Region Institute of Traditional Chinese Medicine (Xinjiang Medical University Affiliated Hospital of Traditional Chinese Medicine, a grade III level A teaching hospital). Adolescents with mild-to-moderate myopia will be recruited from the 27th Elementary School near the Xinjiang Uygur Autonomous Region Institute of Traditional Chinese Medicine after an ophthalmologic examination. Inclusion criteria will be as follows: the result of retinoscopy is myopic refractive error; distance visual acuity can be corrected to normal using negative spherical or cylindrical lenses; near visual acuity and other visual functions must be normal; myopia diopter spherical lenses must be between -0.5 D and -6.00 D, and cylindrical lenses <1.5 D, as measured under cycloplegia; and adolescents must be between seven and 12 years of age. Exclusion criteria will be as follows: subjects with serious systemic diseases, such as cerebrovascular, liver, kidney, hematopoietic system, and psychiatric diseases; long-term use of other related drugs or treatments, which have not been terminated; diopter < -0.5 D, or combined with pathologic myopia-related fundus changes and/or significant visual function impairment; and the affected eyes have other diseases which affect the determination of acupuncture efficacy.

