### Sample size and statistical analysis

#### Sample size

Based on the myopia diopter described in the literature
[27], the sample size will be estimated using the formula for superiority test sample size for two quantitative samples
[28]. The inspection significance level α = 0.05 (two-sided) with a combined standard deviation (S) of 0.25, will be obtained according to the literature, where *u*_1*-α*_, *u*_1-β_ are the bounds of the one-sided standard normal deviation, *u*_1–0.05_ = 1.645, and *u*_1-o.20_ = 0.845. *δ*_u_ is the effective boundary (*δ*_u_ >0), assuming *δ*_u_ = 0.2; θ is the estimate of the overall mean difference value of the acupuncture and control groups, and will be set at 3.0 according to the literature
[27]. By substitution into the above formula with n = 79 and an expected dropout rate of 20%, a total of 100 cases will be included. The sample ratio between the groups will be 1:1.

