### Statistical analysis

All statistical analyses will be performed using SPSS 17.0 statistics software. For quantitative data, the distribution pattern and homogeneity of variance will be examined. If there is a symmetric distribution, the mean (M) ± standard deviation will be used for statistical description, otherwise the M interquartile range (IQR) will be used to describe the trend of concentration and amount of scatter. If this condition is met, the Student's t-test will be used to compare the differences between the quantitative indices between the groups, otherwise the Wilcoxon rank-sum test will be used. For categorical data (binary classification and multiple classification), the composition ratio will be used for statistical description. Based on the observation of a theoretical frequency distribution, the χ^2^ or Fisher's exact test will be used, depending on the specific situation. The ranked data will be analyzed using the Wilcoxon rank-sum test.

Primary and secondary outcomes will be analyzed by the superiority test in accordance with the principle of intention-to-treat, using Per Protocol Set (PPS) and Full Analysis Set (FAS) datasets. The indices of safety evaluation will be analyzed using the Save Set (SS) dataset. The significance level in this study will be set at α = 0.05, and the one-sided test will be used. The detailed statistical analytical methods for primary and secondary outcomes and baseline data are shown in Table 
2 (variables, measures, and methods of analysis).

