**Table 2 Tab2:** **Variables, measures, and methods of analysis**

Variable/outcome	Hypothesis	Outcome measure	Methods of analysis
1) Primary	Intervention improved outcome from baseline to 7 days	Adherence% (>80%) [binary]	
Diopter	Diopter reduced or increased after treatment	Diopter [continuous]	t-test (rank-sum test) or repeated measurement
2) Secondary	Intervention improved outcome from baseline to 7 days	Adherence% (>80%) [binary]	
Visual acuity	Visual acuity did not increase or decrease after treatment	Visual acuity changes [continuous]	t-test (rank-sum test) or repeated measurement
Axial length	Axial length was not increased	Axial length changes [continuous]	t-test (rank-sum test) or repeated measurement
Lens thickness	Lens thickness was not increased	Lens thickness changes [continuous]	t-test (rank-sum test) or repeated measurement
Ciliary body thickness	Ciliary body thickness was not increased	Ciliary body thickness changes [continuous]	t-test (rank-sum test) or repeated measurement
Eye symptoms and systemic symptoms	No adverse symptoms	No adverse symptoms	Chi-squared test or Fisher’s exact test
Compliance	Compliance	Cure rate [binary]	Chi-squared test or Fisher’s exact test
Combination therapy/treatment	Improvement occurred	Whether other drugs were used during treatment [binary]	Chi-squared test or Fisher’s exact test
Adverse event	Improvement occurred	Presence of drug-related adverse event [binary]	Chi-squared test or Fisher’s exact test
3) Baseline analyses:		Adherence% (>80%) [continuous]	
Age		CRF [continuous]	t-test (rank-sum test)
Weight and height		CRF [continuous]	t-test (rank-sum test)
Female versus male		CRF [binary]	Chi-squared test or Fisher’s exact test
Race		CRF [more categories]	Chi-squared test or rank-sum test
Birth weight		CRF [continuous]	t-test (rank-sum test)
Preterm children		CRF [binary]	Chi-squared test or Fisher’s exact test
Parental myopia or not		CRF [binary]	Chi-squared test or Fisher’s exact test
Sibling myopia or not		CRF [binary]	Chi-squared test or Fisher’s exact test
Daily close reading time		CRF [continuous]	t-test (rank-sum test)
Outdoor time		CRF [continuous]	t-test (rank-sum test)
Eye exercises every day or not		CRF [binary]	Chi-squared test or Fisher’s exact test
Daily sleep time		CRF [continuous]	t-test (rank-sum test)
Room light conditions		CRF [binary]	Chi-squared test or Fisher’s exact test
Poor reading habits		CRF [more categories]	Chi-squared test or rank-sum test

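### Table 2 leaves open an unadjusted comparison of follow-up diopter levels for the primary outcome, although the planning SD of 0.25 fits only change or a baseline-adjusted residual

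*Protocol article*

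**What the plan says.** The Statistical analysis section refers to Table 2 for the detailed methods. Table 2 gives the primary outcome measure as "Diopter [continuous". Visual acuity and axial length appear as "Visual acuity changes [continuous" and "Axial length changes [continuous", and lens thickness and ciliary body thickness are also listed as changes. The hypothesis for the primary row is "Diopter reduced or increased after treatment", and its method is "t-test (rank-sum test) or repeated measurement".

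The text of the Statistical analysis section says that, if the distributional conditions are met, "the Student's t-test will be used to compare the differences between the quantitative indices between the groups"; otherwise the Wilcoxon rank-sum test is used. It sets a one-sided test at 0.05.

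Under Recruitment, "myopia diopter spherical lenses must be between -0.5 D and -6.00 D". Table 1 shows diopter measured at baseline and at all three follow-up visits. The Randomization section describes 1:1 allocation and mentions no stratification by baseline diopter. The Sample size section uses a "combined standard deviation (S) of 0.25" taken from the literature and does not say whether it refers to levels or to change.

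**The concern.** Within one table, four ocular outcomes are defined as changes and the outcome that decides the trial is not. No listed method names baseline diopter, although every child has it measured. An analyst could follow Table 2 to the letter and compare mean follow-up diopter between arms with a t-test.

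That comparison would carry the full spread between children at entry. A child who starts at -5 D and one who starts at -1 D differ by far more than two months of treatment is likely to move either of them, if the expected effect is tenths of a diopter. The SD of 0.25 behind the sample size would then describe a different quantity from the one tested, and the trial would be much less able to detect its planned difference.

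**Working it through.** **1. The plan's own sample size.** Inputs from the Sample size section: S = 0.25, boundary 0.2, θ = 3.0, normal deviates 1.645 and 0.845.

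n per group = 2 × S² × (1.645 + 0.845)² / (θ − 0.2)²

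- Printed θ = 3.0: 2 × 0.0625 × 6.2001 / 2.8² = 0.775 / 7.84 = 0.099, i.e. 1 per group. The stated n = 79 is not reproduced.
- θ = 0.3: 0.775 / 0.1² = 77.5, i.e. 78 per group, close to 79.

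So 0.3 D is inferred as the intended difference; it is not printed anywhere. The 78 is a per-group number, whereas the article's step from 79 to 100 (79 / 0.80 = 98.75) treats 79 as a total. That is a separate matter. Here I take the size the trial will have: 50 per arm less 20% dropout = 40 evaluable per arm.

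**2. Can 0.25 be the SD of levels?** With an SD of 0.25, a band of ±2 SD is 1.0 D wide. The entry range is 6.00 − 0.5 = 5.5 D wide. The SD of levels is not in the document, so I assume a range. A uniform spread gives 5.5/√12 = 1.59 D, range/4 gives 1.375 D and range/6 gives 0.92 D. I extend the lower end to 0.8 D to be generous to the plan.

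**3. Power of a raw comparison.** SE = SD × √(2/40). Power = Φ(difference/SE − 1.645), one-sided 0.05. The detectable difference at 80% power is 2.487 × SE.

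| SD (D) | SE (D) | Power, 0.3 D against zero | Power, 0.3 D against the 0.2 boundary | Detectable difference (D) |
|---|---|---|---|---|
| 0.25 | 0.056 | >99% | 56% | 0.14 |
| 0.8 | 0.179 | 51% | 14% | 0.44 |
| 1.0 | 0.224 | 38% | 12% | 0.56 |
| 1.375 | 0.307 | 25% | 9% | 0.76 |
| 1.59 | 0.356 | 21% | 9% | 0.88 |

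The standard error grows by 0.8/0.25 = 3.2 to 1.59/0.25 = 6.4 times. The 56% in the first row reflects the sample-size problem in step 1, not the choice between level and change.

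**4. What baseline adjustment recovers.** Suppose 0.25 is the SD of change and the level SD is equal at both visits. Then the baseline to follow-up correlation is ρ = 1 − 0.25²/(2 × SD²).

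- SD 0.8: ρ = 1 − 0.0625/1.28 = 0.951; ANCOVA residual SD = 0.8 × √(1 − 0.951²) = 0.25.
- SD 1.59: ρ = 1 − 0.0625/5.056 = 0.988; residual SD = 1.59 × √(1 − 0.988²) = 0.25.

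On that reading, a change score or ANCOVA returns to the planning SD.

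**5. Chance baseline imbalance.** With 50 per arm, the SE of the baseline mean difference is SD × √(2/50) = 0.2 × SD. The chance of a difference of at least 0.3 D in either direction is 6% at SD 0.8 (0.3/0.16 = 1.88) and 35% at SD 1.59 (0.3/0.318 = 0.94).

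**The case against.** The strongest reply is that Table 2 does not commit to an unadjusted t-test. It also allows repeated measurement, and a repeated-measures analysis that includes the baseline visit uses baseline through the group-by-time term. The hypothesis wording speaks of movement after treatment, and the header row above it refers to improvement from baseline. If 0.25 makes sense only for change, the planners probably meant change, and Table 2 is loosely worded. The article is condensed, and a statistical analysis plan that is not shown may settle the model.

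Much of this stands. A reader might infer that the plan fixes an unadjusted test of levels; it does not, it leaves that test open. But the repeated-measures option names no baseline term or contrast, and modelling only post-treatment levels would not help. The article does list variables and tests outcome by outcome, and the mismatch lies in what it lists.

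Three further inferences should be resisted.

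- **That entry spread swamps the planned effect whatever its size.** Against the printed θ of 3.0, or 2.8 after the boundary, power is about 100% even at an SD of 1.59. The loss arises for a difference of tenths of a diopter.
- **That the raw comparison is biased.** Randomisation keeps it unbiased, and its standard error already includes chance imbalance.
- **That a baseline imbalance as large as the effect is likely.** The chance is about 6% to 35%.

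**Conclusion.** The point holds as a defect of definition with a real cost in precision. The primary variable is not stated to be a change, the method is left open with no baseline term, and the planning SD does not suit the variable as listed. If levels were compared, power for 0.3 D against zero would be about 51% to 21% rather than over 99%.

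These figures rest on three assumptions: a level SD of 0.8 to 1.59 D inferred from the entry range, 40 evaluable children per arm, and a true difference of 0.3 D inferred from the stated n. What the 0.25 measures depends on a cited source that is not at hand. The direction of the conclusion does not depend on the exact SD: any level SD well above 0.25 breaks the link between the sample size and the test.

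**What to change.** - In Table 2, define the primary variable as change from baseline in cycloplegic diopter, in line with the wording already used for the secondary ocular measures.
- In Table 2 and the Statistical analysis section, replace the open choice with one method: ANCOVA, or a repeated-measures mixed model, with baseline diopter as covariate.
- In the Sample size section, state that S is the SD of that quantity.

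Adding age as a covariate, or keeping the rank-sum test only as a sensitivity analysis, is optional and not needed to close this point.

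The cost is wording in Table 2 and two paragraphs. Baseline diopter is already collected, so no new data are needed. The Trial status section reports six participants recruited, so the change can be made early, with notification as the article's section on protocol amendments requires.

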### Secondary outcomes

The secondary outcomes in this study will include distance visual acuity
[22], AL
[17], lens thickness
[18], and ciliary body thickness
[19]. These indices will be measured before treatment, and at the first, third, and sixth months after two months of treatment. The objective examinations will be recorded in the CRFs. The main time points of evaluation will be the sixth month after treatment or when the trial is terminated.

Distance visual acuity will be measured using a standard logarithmic visual acuity test chart (TR-B; Tongrui Medical Equipment Co., Ltd., Tianjin, China), under sufficient lighting to measure the parameters of visual acuity, with a 5-m distance to the visual acuity test chart. All visual acuity examinations in this study will be carried out by one nurse in a fixed place who will not participate in acupuncture treatment or clinical examinations. The specific details of the subjects will not be disclosed to the nurse.

In order to measure AL and lens thicknesses, the subject will be placed in the supine position. Oxybuprocaine Hydrochloride Eye Drops (20 ml, Santen Pharmaceutical Co. Ltd. Suzhou, China) will be applied to the eye to be examined, and topical anesthesia will be applied. The subjects will be asked to watch the red light at the top of the probe with the eye to be examined. A disinfected ultrasound probe will be placed on the surface of the cornea. Sound waves will pass through the middle of the corneal vertex, the center of the lens, and the vitreous body, to reach the macular fovea. The sound beam will be kept in a vertical orientation. The AL and lens thicknesses will be measured. Ten sets of values will be selected, with a measurement error within 0.1 mm
[22]. The lens thickness is the axial distance from the front surface to the posterior surface of the lens
[19, 23]. An ophthalmic ultrasound instrument (CINESCAN; Quantal Medical, Paris, France) will be used for these measurements in the proposed study. Ten measurements of a particular index will usually be made, and these 10 measurements will be recorded and the average value obtained. The AL and lens thickness measurements will be carried out by one full-time physician, on a fixed instrument, and at a fixed location. The physician will not participate in visual acuity examinations and acupuncture treatment, and the specific details with respect to the grouping of subjects will not be disclosed to the physician.

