In order to measure ciliary body thickness, oxybuprocaine hydrochloride eye drops will be applied to the eye to be examined. After topical anesthesia is applied, a disinfected eye cup of appropriate size will be placed beneath the upper eyelid. At this time, the subjects will be asked to move the eye downward to prevent scratching the cornea. The lower eyelid will then be pulled. The eye cup will be placed beneath the lower eyelid, so that it is immobilized between the eyelids and the eyeball. Distilled water will be poured into the eye cup. The contralateral eye will gaze at the red indicator light on the nasal side. An ultrasound biomicroscope (MD-300 L; Meda Co. Ltd., Tianjin, China) will be used. A 50 mhz transducer with 4 to 5 mm tissue penetration depth will be used to measure ciliary body thickness at the temporal corneoscleral limbus of the eye to be examined. The image will then be obtained. The built-in ruler will be used to measure ciliary body thickness (vertical distance) 2 mm behind the scleral spur
[24, 25]. The position of the bilateral temporal side (nine points in the right eye, three points in the left eye) will be measured once manually and the results will be recorded. The same instrument will be used for all measurements. The measurement of ciliary body thickness in this research will be completed by one full-time physician, using a fixed instrument, in a fixed place. The physician will not participate in visual acuity examinations or acupuncture treatment, and the specific details of the subjects will not be disclosed to the physician.

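### Table 2 tests the four secondary eye outcomes as unadjusted change scores; this is valid, but in general less precise than adjusting for the baseline value already collected

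*Protocol article*

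**What the plan says.** In Table 2 the outcome measures for the four secondary eye variables are "Visual acuity changes [continuous", "Axial length changes [continuous", "Lens thickness changes [continuous" and "Ciliary body thickness changes [continuous". The method in each of these rows is "t-test (rank-sum test) or repeated measurement". The Statistical analysis section gives the general rule that "the Student's t-test will be used to compare the differences between the quantitative indices between the groups", with the Wilcoxon rank-sum test as fallback, and sends the reader to Table 2 for the detailed methods. Neither place names the baseline value as a covariate.

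The baseline values will exist. The Secondary outcomes section states: "These indices will be measured before treatment, and at the first, third, and sixth months after two months of treatment". Table 1 shows the same baseline collection.

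The same section describes how the readings are taken. Axial length and lens thickness are averages of ten readings. Ciliary body thickness "will be measured once manually and the results will be recorded". The Background says that visual acuity is open to many outside influences.

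**The concern.** A change score subtracts the baseline with a fixed coefficient of 1. The best coefficient is the slope b of follow-up on baseline, which ANCOVA estimates from the data. Where b is below 1, the change score over-corrects. Baseline noise enters the outcome, and an arm that happens to start high tends to show a larger fall even without a treatment effect.

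At stake is the precision of four secondary comparisons in a trial of 100 children, with no stratification by baseline described. The loss is avoidable, because the baseline readings are collected anyway.

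**Working it through.** The plan states no figure on this point. Its sample size concerns diopter only, so there is nothing to reproduce first.

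**Inputs**
- Arms: 50 each (Study design). With the 20% dropout in the Sample size section, 50 × 0.8 = 40 evaluable per arm.
- Test level: one-sided 0.05 (Statistical analysis).
- Correlation r between baseline and follow-up: not in the documents. Assumed range 0.5 to 0.98.
- Ratio k of follow-up SD to baseline SD: not in the documents. Assumed 1, then varied.

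**General result.** Set the baseline SD to 1, so that b = rk. Per child:
- Var(change) = 1 + k² − 2rk
- Var(ANCOVA) = k²(1 − r²)
- Difference = (1 − rk)² = (1 − b)²

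The change score is therefore never more precise, apart from the one degree of freedom spent on the covariate. The two are equal when b = 1. Given a chance baseline difference D between arms, the change-score estimate shifts by −(1 − b)D.

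**Equal SDs (k = 1, so b = r).** Var(change) = 2(1 − r) and Var(ANCOVA) = 1 − r², so the ratio is (1 + r)/2. The extra children needed for equal precision are 2/(1 + r) − 1. If ANCOVA had 80% power, the change score would have Φ(2.487 × √((1 + r)/2) − 1.645), where 2.487 = 1.645 + 0.842. With 40 per arm, the SD of a chance baseline difference is √(2/40) = 0.22 baseline SD. The last column is −(1 − r) × 0.22.

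| r | Variance ratio | Extra children | Change-score power if ANCOVA has 80% | Shift for D = 0.22 SD |
|---|---|---|---|---|
| 0.5 | 0.75 | 33% | 69% | −0.11 SD |
| 0.7 | 0.85 | 18% | 74% | −0.07 SD |
| 0.9 | 0.95 | 5% | 78% | −0.02 SD |
| 0.98 | 0.99 | 1% | 80% | −0.004 SD |

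**Simulation** (40 per arm, 6,000 trials for each r, equal SDs). The variance ratios were 0.75, 0.87, 0.95 and 1.01. At r = 0.98 the small theoretical gain is thus not visible once the slope has to be estimated. The correlation of the change-score estimate with the baseline difference was −0.51, −0.38, −0.24 and −0.10. For ANCOVA it was about 0. With no treatment effect simulated, both estimators averaged about 0.

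**Unequal SDs.** At r = 0.9 and k = 1.1, b = 0.99. Var(change) = 1 + 1.21 − 1.98 = 0.23 and Var(ANCOVA) = 1.21 × 0.19 = 0.2299, so the ratio is about 1.00 and nothing is lost. At r = 0.9 and k = 0.9, b = 0.81. Var(change) = 1 + 0.81 − 1.62 = 0.19 and Var(ANCOVA) = 0.81 × 0.19 = 0.1539, a ratio of 0.81. The slope governs the loss, not the correlation alone.

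**The case against.** The strongest reply is that nothing here is wrong. A two-group comparison of change is a standard, valid analysis and matches the hypotheses in Table 2, which are worded as a measure not having increased. A reader might infer from the carry-over of imbalance that the result is biased or that false positives become more likely. Neither follows. Over randomisations the estimate is unbiased, and its standard error already allows for chance imbalance. The shift is conditional on the imbalance that happens to be observed. This part of the reply stands.

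A second reply is that the repeated-measures option leaves the model open, and that covariates may be set in an analysis plan not shown. This stands in part. That route does not exclude a baseline covariate, and a change outcome with a baseline covariate gives the same arm effect as ANCOVA on follow-up. But the other route in the same cell is a t-test or rank-sum test on the change, which uses no covariate, and the article presents Table 2 as its detailed methods. The unadjusted change score is thus a stated choice.

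A third reply is that the size is assumed. This also stands. A single manual reading and a general remark about acuity suggest noise, but without the between-child spread they do not show a low correlation. The article also standardises both measures: one physician and a fixed instrument for ciliary body thickness, and one nurse in a fixed place for acuity. A reader might take a loss of a third as established for these two outcomes; the documents do not support that. Nor is any planned power lost, because the sample size does not cover the secondary outcomes and the 80% reference above is hypothetical.

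**Conclusion.** The point holds as one of efficiency. For the four secondary eye outcomes, Table 2 uses the baseline in a form that is in general less precise than adjustment, and no baseline covariate is named.

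With equal SDs and r between 0.5 and 0.98, the change score would need from 33% down to 1% more children for the same precision. Both r and the equal-SD condition are assumptions. Where the slope is near 1, which may hold for axial length, the gain is about nil. For ciliary body thickness and visual acuity it could be larger, but the documents do not let one say by how much.

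It would be too strong to say that a change score is efficient only when the correlation is almost perfect: the condition is a slope of 1, which can also arise at a lower correlation if the spread grows over time. The change is worth making because it costs almost nothing, but it concerns secondary outcomes and does not threaten validity.

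**What to change.** In Table 2, for each of the four outcomes:
- Name ANCOVA as the analysis: the follow-up value (or, equivalently, the change) at the main time point given in the Secondary outcomes section, regressed on arm, with that measure's own baseline value as covariate.
- If the repeated-measures option is used, include the baseline value as a covariate there too.
- Report the adjusted mean difference with its confidence interval.
- Keep the rank-sum test on change as a sensitivity analysis if residuals are clearly non-normal.
- Mean change may stay as a descriptive column.

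The cost is one line of analysis wording and one degree of freedom per model. No new data, visits or children are needed.

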**Methods/Design:**

A randomized, parallel, single-center, assessor- and statistician-blinded, controlled clinical trial will be performed. A total of 100 teenagers, between seven and 12 years of age, with mild-to-moderate myopia and spherical lenses <-6.00 D and cylindrical lenses <-1.50 D will be selected from the Xinjiang Uygur Autonomous Region Institute of Traditional Chinese Medicine, a grade III level A teaching hospital in Urumqi, Xinjiang, China (Xinjiang Medical University Affiliated Hospital of Traditional Medicine). The subjects will be randomly assigned to two different groups (control and acupuncture groups), each group containing 50 subjects. The subjects in both groups wear single-vision corrective lenses. In the acupuncture group, acupuncture will be performed daily for nine consecutive days on five points (bilateral Cuanzhu, Tongziliao, Sibai, Muchuang, and Hegu), followed by no treatment for one day. Six cycles of treatment will be undertaken continuously for a total of 60 days. Following 60 days of treatment, a follow-up period of six months will be included. The primary outcome will be diopter determination. The secondary outcomes will include distance visual acuity, axial length, lens thickness, ciliary body thickness, and subjective symptoms of the eyes and entire body. The main time points for the evaluation of clinical efficacy will be the first, third, and sixth months after treatment.

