**Table 1 Tab1:** **Time of visit and data collection**

Data obtained/recorded	Baseline	Treatment phase	Visit 1	Visit 2	Visit 3
	-7 days	1-2 months	3 months	5 months	8 months
Signed informed consent	×				
Medical history	×				
Met the diagnostic standard/exclusion criteria	×				
General record	×				
Diagnosis	×				
Visual acuity	×		×	×	×
Diopter	×		×	×	×
Axial length	×		×	×	×
Lens thickness	×		×	×	×
Ciliary body thickness	×		×	×	×
Skin damage	×	×	×	×	×
Eye symptoms and systemic symptoms	×	×	×	×	×
Randomization	×				
Group therapy	×				
Case report form	×		×	×	×
Adverse event		×	×	×	×
Close-out					×

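### Table 2 scores eye and systemic symptoms as absence of adverse symptoms with no stated baseline reference, so the comparison can show only net prevalence (minor)

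*Protocol article*

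**What the plan says.** The abstract's Methods/Design paragraph closes its list of secondary outcomes with "ciliary body thickness, and subjective symptoms of the eyes and entire body". Table 1 schedules "Eye symptoms and systemic symptoms" at baseline, in the treatment phase and at Visits 1, 2 and 3.

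The Statistical analysis section refers the reader to Table 2 for the detailed methods for primary and secondary outcomes. For symptoms, the hypothesis, outcome measure and method columns read, in order, "No adverse symptoms No adverse symptoms Chi-squared test or Fisher’s exact test". Hypothesis and measure are the same phrase. The row names no visit, carries no binary tag and makes no reference to baseline.

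The rows around it differ. Visual acuity, axial length, lens thickness and ciliary body thickness are each scored as changes, for example "Axial length changes [continuous" in the axial length row. Adverse events have a row of their own, with the measure "Presence of drug-related adverse event [binary". The heading row over the secondary block reads "Intervention improved outcome from baseline to 7 days".

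The Secondary outcomes section, which begins "The secondary outcomes in this study will include distance visual acuity", goes on to the three ocular dimensions. It neither lists symptoms nor gives a scoring rule for them.

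**The concern.** The outcome is listed among the efficacy measures but worded as a harm. Without a baseline reference, the natural way to apply the row is to classify each child as with or without symptoms after treatment and compare the two proportions.

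Under that rule, a child whose eye strain is unchanged since entry scores the same as a child with a new complaint. A child whose eye strain has gone scores the same as one who never had any. The result then measures neither relief nor new harm.

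The trial sets out to confirm both effectiveness and safety. If acupuncture eased some existing complaints and caused some new ones, the two effects would move the same proportion in opposite directions, and a report of no difference could hide both.

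**Working it through.** The article gives no symptom rate, effect or power for this outcome, so there is no figure to reproduce. The check asks what a present-versus-absent comparison after treatment can detect.

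**Inputs from the article**
- 50 children per arm, 1:1 (Randomization).
- 20% expected dropout (Sample size), hence 50 × 0.8 = 40 per arm.
- Chi-squared or Fisher's exact test (Table 2).

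**Assumed inputs**
- b: share symptomatic at baseline.
- r: share of those who resolve.
- q: share of baseline-free children who develop a symptom.

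**Formula.** Post-treatment prevalence in an arm = b(1 − r) + (1 − b)q. The test sees this sum, not its two parts.

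**Exact cancellation.** Let controls stay at b = 0.40. Under acupuncture, take r = 0.50 and q = 0.333:
- 0.40 × 0.50 + 0.60 × 0.333 = 0.20 + 0.20 = 0.40.
- The arms are equal, so the pooled test rejects at no more than about its nominal level, whether one-sided or two-sided.
- Split by baseline status (two-sided 0.05), approximate power is 0.95 (40 per arm) to 0.98 (50 per arm) for resolution, and 0.90 to 0.95 for new onset.
- With controls unchanged, exact cancellation requires q = br/(1 − b). Over b = 0.2 to 0.6 and r = 0.25 to 0.50, q runs from 0.06 to 0.75.

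**Less extreme rates.** Assume 90% of baseline symptoms persist and 5% of baseline-free children develop one in controls. Harm means 25% new onset under acupuncture. Benefit means 50% persistence under acupuncture. Power is by simulation, 50 per arm, two-sided 0.05, good to about two percentage points:

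| Scenario | Baseline prevalence | Present vs absent | Split by baseline |
|---|---|---|---|
| Harm only | 20 / 40 / 60% | 42 / 24 / 14% | 76 / 61 / 41% (baseline-free children) |
| Benefit only | 20 / 40 / 60% | 17 / 43 / 70% | 52 / 83 / 95% (symptomatic children) |
| Both | 40% | 7% | 60% harm, 82% benefit |

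Check of the last row:
- Control: 0.4 × 0.9 + 0.6 × 0.05 = 0.39.
- Acupuncture: 0.4 × 0.5 + 0.6 × 0.25 = 0.35.
- A 20-point harm and a 40-point benefit, each in its own subgroup, leave a 4-point net difference.

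At 40 per arm the last row becomes about 6% against 53% and 72%.

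**Limits of the illustration**
- Cancellation is not general. With both effects at 60% baseline prevalence, prevalence is 0.6 × 0.9 + 0.4 × 0.05 = 0.56 against 0.6 × 0.5 + 0.4 × 0.25 = 0.40, and the present-versus-absent test has about 39% power.
- In the harm-only case, the drop from 20 points to 16 / 12 / 8 points is a change of denominator. At 40% prevalence, 20% of 30 baseline-free children and 12% of all 50 are the same 6 extra cases. The power is lost because persisting complaints add noise.
- A Mantel-Haenszel test stratified by baseline status has about 8% power when both effects are present at 40%. It still combines two opposing effects into one.

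**The case against.** A reader might infer that the plan discards the baseline symptom record. The article does not say so. The row is silent, the block heading mentions baseline, Table 1 collects the record, and the word adverse could mean newly arising. Coding detail of this kind may also sit in an analysis plan or case report form that is not shown. What stands is that non-use cannot be asserted. But the article presents Table 2 as its detailed methods, and that table writes a change measure where one is meant. The block heading's 7-day horizon matches no follow-up visit in Table 1 and gives no scoring rule. Reading the row as new symptoms only would drop the efficacy outcome in the abstract and overlap with the adverse event row.

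A reader might also infer bias. There is none in expectation: randomization balances baseline symptoms, and the difference in post-treatment prevalence is a valid net effect. What suffers is interpretability and precision.

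Nor does it follow that harm would go unseen, since adverse events are recorded and analysed in their own row.

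On the numbers, every rate is assumed, and nothing in the article suggests two sizeable effects that happen to balance. The power table uses a two-sided test, whereas the article states "The significance level in this study will be set at α = 0.05, and the one-sided test will be used". The trial is sized on diopter, so modest power on a symptom item is expected under any scoring. These objections limit the magnitude. They do not give the row a baseline reference.

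**Conclusion.** The point holds in a limited form. Table 2 sets a secondary outcome as absence of adverse symptoms, under an unadjusted two-group test, without saying how complaints already present at entry count. Read as present versus absent after treatment, it yields an unbiased net prevalence that separates neither relief from new onset nor old complaints from new ones.

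The loss could run from slight to nearly complete, depending on baseline prevalence, resolution and onset rates that the article does not give. The power figures therefore show what can happen, not what is expected. As this is a secondary outcome with adverse events handled separately, the priority is minor.

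**What to change.** Replace the symptom row in Table 2 with two rows, each compared between arms at a named scheduled visit:

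1. **Efficacy:** resolution or improvement among children symptomatic at baseline.
2. **Safety:** symptoms new or worse than at baseline, reported alongside the adverse event row.

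If severity is not graded on the case report form, use resolution and new onset only. If one overall proportion is kept as well, stratify it by baseline symptom status (Mantel-Haenszel), and state that this improves precision but does not separate opposing effects.

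The cost is a wording change and one more table. Table 1 already schedules the data, and the Trial status section reports six participants recruited, so the change could precede any results.

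There are downsides. Each measure uses a subset or adds a secondary comparison. If only 20% of children are symptomatic at baseline, the efficacy measure rests on about 0.2 × 50 = 10 per arm. With no sham arm, symptom reports remain unblinded under either scoring.
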